### 8.12 Name and description of each Non-Investigational Medicinal Product (NIMP)

All participants will be receiving an OBT at screen which may consist of any cART regimen which has achieved a sustained undetectable HIV VL.

## 9. PHARMACOVIGILANCE

### 9.1 Definitions

| Term                         | Definition                                                                                                                                                                                                                                                                                                                                                                                                                                                                                                                                                                                                |
|------------------------------|-----------------------------------------------------------------------------------------------------------------------------------------------------------------------------------------------------------------------------------------------------------------------------------------------------------------------------------------------------------------------------------------------------------------------------------------------------------------------------------------------------------------------------------------------------------------------------------------------------------|
| Adverse Event (AE)    | Any untoward medical occurrence in a participant to whom a medicinal product has been administered, including occurrences which are not necessarily caused by or related to that product.                                                                                                                                                                                                                                                                                                                                                                                                                 |
| Adverse Reaction (AR) | 
An untoward and unintended response in a participant to an investigational medicinal product which is related to any dose administered to that participant.
 
The phrase "response to an investigational medicinal product" means that a causal relationship between a trial medication and an AE is at least a reasonable possibility, i.e. the relationship cannot be ruled out.
 
All cases judged by either the reporting medically qualified professional or the Sponsor as having a reasonable suspected causal relationship to the trial medication qualify as adverse reactions.
 |

|                                                              |                                                                                                                                                                                                                                                                                                                                                                                                                                                                                                                                                                                                                                                                                                                                                                                                                                                              |
|--------------------------------------------------------------|--------------------------------------------------------------------------------------------------------------------------------------------------------------------------------------------------------------------------------------------------------------------------------------------------------------------------------------------------------------------------------------------------------------------------------------------------------------------------------------------------------------------------------------------------------------------------------------------------------------------------------------------------------------------------------------------------------------------------------------------------------------------------------------------------------------------------------------------------------------|
| Serious Adverse Event (SAE)                           | 
A serious adverse event is any untoward medical occurrence that:
 
 
• results in death
 
• is life-threatening
 
• requires inpatient hospitalisation or prolongation of existing hospitalisation
 
• results in persistent or significant disability/incapacity
 
• consists of a congenital anomaly or birth defect
 
 
Other ‘important medical events’ may also be considered serious if they jeopardise the participant or require an intervention to prevent one of the above consequences.
 
NOTE: The term "life-threatening" in the definition of "serious" refers to an event in which the participant was at risk of death at the time of the event; it does not refer to an event which hypothetically might have caused death if it were more severe.
 |
| Serious Adverse Reaction (SAR)                        | 
An adverse event that is both serious and, in the opinion of the reporting Investigator, believed with reasonable probability to be due to one of the trial treatments, based on the information provided.
                                                                                                                                                                                                                                                                                                                                                                                                                                                                                                                                                                                                                                            |
| Suspected Unexpected Serious Adverse Reaction (SUSAR) | 
A serious adverse reaction, the nature and severity of which is not consistent with the information about the medicinal product in question set out:
 
 
• in the case of a product with a marketing authorisation, in the summary of product characteristics (SmPC) for that product
 
• in the case of any other investigational medicinal product, in the investigator’s brochure (IB) relating to the trial in question
 
                                                                                                                                                                                                                                                                                                                                                                      |

NB: to avoid confusion or misunderstanding of the difference between the terms “serious” and “severe”, the following note of clarification is provided: “Severe” is often used to describe intensity of a specific event, which may be of relatively minor medical significance. “Seriousness” is the regulatory definition supplied above. For example, a headache may be severe in intensity but would not be classified as serious unless it met one of the criteria for serious events.

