### **Assessment of Intensity**

Severity should be recorded and graded according to the AIDS Clinical Trial Group (ACTG) Grading Scale (Appendix 2).

All events deemed to be Grade 4 (potentially life threatening) according to the ACTG grading scale should be routinely reported as a serious adverse event. However there may be occasions where in the investigator's clinical judgement they do not consider the event to be life threatening; therefore they do not consider the event to meet the definition of an SAE. In these cases the investigator must document clearly in the participants source documentation that the Grade 4 event has been assessed and why in their clinical judgement they do not consider the event to be life threatening.

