| Fever (nonaxillary)                                                                                                                                                            | 37.7 – 38.6°C                                                                         | 38.7 – 39.3°C                                                                                | 39.4 – 40.5°C                                                              | > 40.5°C                                                                                                                             |
| Pain (indicate body site)

DO NOT use for pain due to injection
(See Injection Site Reactions: Injection site pain)

See also Headache, Arthralgia, and Myalgia | Pain causing no or minimal interference with usual social & functional activities     | Pain causing greater than minimal interference with usual social & functional activities     | Pain causing inability to perform usual social & functional activities     | Disabling pain causing inability to perform basic self-care functions OR Hospitalization (other than emergency room visit) indicated |

**Basic Self-care Functions – Adult:** Activities such as bathing, dressing, toileting, transfer/movement, continence, and feeding.

**Basic Self-care Functions – Young Children:** Activities that are age and culturally appropriate (e.g., feeding self with culturally appropriate eating implement).

**Usual Social & Functional Activities – Adult:** Adaptive tasks and desirable activities, such as going to work, shopping, cooking, use of transportation, pursuing a hobby, etc.

**Usual Social & Functional Activities – Young Children:** Activities that are age and culturally appropriate (e.g., social interactions, play activities, learning tasks, etc.).

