#### Footnotes

 PI or delegate.

 Notable or safety critical events must be reported as per protocol.

 Sponsor cannot downgrade the PI's causality assessment, but can upgrade it.

 Reference Safety Information (RSI) in IB or SmPC.

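### Protocol Section 9 contradicts itself on which serious events count as suspected reactions and on when a Grade 4 event may be treated as not serious

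*Protocol*

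**What the plan says.** **Causality.** For an AR, Protocol 9.1 requires that "a causal relationship between a trial medication and an AE is at least a reasonable possibility, i.e. the relationship cannot be ruled out". It also says whose view counts: "All cases judged by either the reporting medically qualified professional or the Sponsor as having a reasonable suspected causal relationship" qualify. For a SAR, the same table requires that the event be serious and, in the view of the reporting investigator alone, "believed with reasonable probability to be due to one of the trial treatments". A SUSAR is then defined through the SAR, as "A serious adverse reaction, the nature and severity of which is not consistent with" the product information. Section 9.2 grades causality on five levels, with *possible* and *probable* kept apart.

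Section 9.3 has its own classification rule. An SAE that the PI, a delegate or the CI on central review suspects to be related, and that is unexpected, becomes a SUSAR. The closing line of 9.3 nevertheless sends expedited reporting back to SUSARs as 9.1 defines them. Appendix 3, footnote 3, adds: "Sponsor cannot downgrade the PI's causality assessment, but can upgrade it".

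**Seriousness.** Section 9.1 lists five criteria (death, threat to life, hospitalisation, disability, congenital anomaly) and adds important medical events. Section 9.2 (Assessment of Intensity) makes every Grade 4 event an SAE by default. It then describes an exception for cases where, in the investigator's judgement, "they do not consider the event to be life threatening; therefore they do not consider the event to meet the definition of an SAE". The source note has to explain only why life was not threatened.

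**The concern.** On the SAR wording, the causality threshold rises as the event becomes more serious: a non-serious event qualifies as a reaction on a reasonable possibility, a serious one only on a reasonable probability. The set of people whose opinion counts also shrinks, from reporter or Sponsor to reporter alone. Because 9.1 builds the SUSAR on the SAR, two conscientious sites could classify the same unexpected serious event differently, one following 9.1 and the other 9.3. What is at stake is whether that event goes to the regulator and the ethics committee as an expedited report.

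On the Grade 4 wording, the exception draws a conclusion about all of seriousness from a test of one criterion. A site following it to the letter could leave off the 24-hour SAE form an event that 9.1 makes serious on other grounds.

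**Working it through.** No figure is involved, so the check sets the rules side by side and runs cases through them.

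**1. Serious, unexpected event rated *possible***

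| Rule | Test | Result |
|---|---|---|
| AR, 9.1 | reasonable possibility; reporter or Sponsor | met |
| SAE form, 9.3 | any SAE from consent to 30 days after treatment, whatever the causality | reported within 24 hours |
| SAR, 9.1 | reasonable probability; reporting investigator only | not clearly met |
| SUSAR, 9.1 | must first be a SAR | not clearly met |
| SUSAR, 9.3 | SAE suspected to be related, and unexpected | met, if suspected includes *possible* |

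The last two rows disagree. No visible text states which of the five causality levels count as suspected related when a SUSAR is classified. Section 9.3 does count possibly, probably and definitely related events as reactions, but in the sentence on events after the reporting period. It also asks for continued follow-up of SAEs thought possibly related. Both sentences point towards including *possible*; neither is the SUSAR rule.

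**2. Sponsor upgrade.** Appendix 3 lets the Sponsor raise a causality assessment, and the AR definition lets the Sponsor's view alone make an AR. The SAR definition mentions only the reporting investigator, and the 9.3 rule names the PI, a delegate and the CI. The text does not say how an upgrade enters the SAR definition.

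**3. Grade 4 events**

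| Case | SAE under 9.1? | Exempt under 9.2? | Conflict? |
|---|---|---|---|
| Life-threatening | yes | no | no |
| Not life-threatening, no other criterion met | no | yes | no |
| Not life-threatening, another criterion met (e.g. hospitalised) | yes | yes | **yes** |

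Only the third case is in conflict. Appendix 2 shows that it can arise. One of the Grade 4 alternatives for pain is "Hospitalization (other than emergency room visit) indicated", and headache has a similar alternative. The row for clinical events not otherwise listed reaches Grade 4 when intervention is indicated to prevent lasting impairment or disability.

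**4. Extent.** On causality, one of the three levels that 9.3 elsewhere treats as related (*possible*, *probable*, *definite*) is in dispute. On seriousness, there are 5 listed criteria + 1 for important medical events = 6 routes. The exception tests 1 and leaves 6 − 1 = 5 untested, of which hospitalisation, disability and important medical events are the realistic ones for a Grade 4 event.

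**The case against.** The strongest reply is that the operative rules already catch these events. Section 9.3 requires every SAE on the 24-hour form with no causality condition, and Section 9.4 repeats the duty for the PI. The 9.3 SUSAR rule starts from SAEs and does not pass through the SAR definition. Its notion of suspicion echoes the AR definition. The SAR wording is never tied to the scale level *probable*. The trials unit's SOP, to which 9.3 refers, and the Appendix 3 flowchart, whose figure is not available here, may also settle which levels count.

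On Grade 4, the default goes beyond what 9.1 demands, the exception only relaxes that default and needs a documented reason, and the 9.1 definition remains in force. The Appendix 2 rows give hospitalisation as one alternative among others; the hypertension row names life-threatening consequences first.

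Most of this stands, and it rules out several inferences a reader might draw:

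- That serious events rated *possible* miss SAE reporting. They do not.
- That they certainly miss SUSAR reporting. Section 9.3 offers a wider route.
- That a Sponsor upgrade can never produce a SAR. That reading would empty the Appendix 3 footnote of effect. The documents show only a poor fit between the two texts.
- That every Grade 4 event that is not life-threatening is lost. If no other criterion is met, it was never an SAE under 9.1.
- That expedited reports to the DSMB are lost. Section 9.4 sends those reports to the MHRA and the ethics committee; the DSMB receives safety information under the Trial Monitoring Plan.

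The reply does not remove the contradiction. The last line of 9.3 ties expedited reporting to the 9.1 definition, so 9.3 itself carries both the wide rule and the narrow one. An SOP may guide practice, but it would leave the protocol's definitions in conflict. That 9.1 remains in force is also what makes the 9.2 inference wrong: the two sections give opposite answers for the same hospitalised participant.

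**Conclusion.** The point holds as two internal contradictions in safety classification. Under 9.1 and 9.3 together, an unexpected serious event rated *possible* is a SUSAR by one rule and not clearly one by the other. Under 9.1 and 9.2 together, a Grade 4 event that is not life-threatening but meets another seriousness criterion is both an SAE and exempt. Only this second conflict can keep an event off the SAE form.

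The conclusion assumes that sites work from the protocol text and that the SOP and flowchart, which could not be checked, do not override it. The number of events affected cannot be derived from the protocol, and no sample size or efficacy analysis depends on it. The text should be corrected, because these are governing definitions and the repair is small.

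**What to change.** Reconcile the passages using the protocol's own definitions:

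1. In 9.1, define a SAR as any AR, as already defined there (reasonable possibility, in the view of the reporter or the Sponsor), that meets at least one 9.1 seriousness criterion. The SUSAR definition can then stay as it is, and a Sponsor upgrade fits.
2. In 9.3, state that *possible*, *probable* and *definite* all count as suspected related when SUSARs are classified, in line with how 9.3 already treats events after the reporting period.
3. In 9.2, allow the Grade 4 exception only when the investigator documents that none of the 9.1 seriousness criteria, including important medical events, is met.

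The cost is about three sentences in an amendment, a check that the SOP and the Appendix 3 flowchart agree with them, and probably a few more SAE and SUSAR forms.

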## 9.2 Adverse Events and Toxicity Management

Adverse events observed by the Investigator, or reported by the subject, and any remedial action taken, will be recorded in the subject’s eCRF and should be verifiable in the subject’s notes throughout the study. The nature of each event, date of onset, duration and severity will be documented together with the Investigator’s opinion of the causal relationship to the treatment (unrelated, unlikely, possible, probable, and definite).

All subjects experiencing adverse events, whether considered associated with the use of the study medication or not, must be monitored until the symptoms subside and any clinically relevant changes in laboratory values have returned to baseline, or until there is a satisfactory explanation for the changes observed.

Procedures such as surgery should not be reported as adverse events. However, the medical condition for which the procedure was performed should be reported if it meets the definition of an adverse event. For example, an acute appendicitis that begins during the adverse event reporting period should be reported as the adverse event and the resulting appendectomy noted on the eCRF.

Planned procedures such as surgery planned prior to the subject's enrolment into the study need not be reported as adverse events if these are documented as planned at the screening visit.

Clinically significant changes in physical examination and blood safety profiles should also be recorded as adverse events.

An adverse event includes:

- An exacerbation of a pre-existing illness
- An increase in frequency or intensity of a pre-existing episodic event or condition
- A condition detected or diagnosed after trial medication administration even though it may have been present prior to the start of the trial
- Continuous persistent disease/symptoms present at baseline that worsen following the start of the trial

An adverse event does **NOT** include:

- Medical or surgical procedures (e.g. surgery, endoscopy, tooth extraction, transfusion); the condition that leads to the procedure is an AE.
- Pre-existing disease or conditions present at the start of the trial that do not worsen.
- Situations where an untoward medical occurrence has not occurred (e.g. hospitalisations for cosmetic elective surgery/social/convenience admissions).
- HIV-associated conditions or signs/symptoms associated with such conditions unless more severe than expected for the subject's condition.
- Overdose of either antiretroviral agents or concomitant medication without any signs or symptoms.
- A laboratory abnormality that is judged by the investigator not to be of clinical significance

### **Assessment of Intensity**

Severity should be recorded and graded according to the AIDS Clinical Trial Group (ACTG) Grading Scale (Appendix 2).

All events deemed to be Grade 4 (potentially life threatening) according to the ACTG grading scale should be routinely reported as a serious adverse event. However there may be occasions where in the investigator's clinical judgement they do not consider the event to be life threatening; therefore they do not consider the event to meet the definition of an SAE. In these cases the investigator must document clearly in the participants source documentation that the Grade 4 event has been assessed and why in their clinical judgement they do not consider the event to be life threatening.

### **Assessment of Causality**

The relationship to study drug of each adverse event will be assessed using the following definitions:

**DEFINITE:** distinct temporal relationship with drug treatment. Known reaction to agent or chemical group, or predicted by known pharmacology. Event cannot be explained by subject's clinical state or other factors.

**PROBABLE:** reasonable temporal relationship with drug treatment. Likely to be known reaction to agent or chemical group, or predicted by known pharmacology. Event cannot easily be explained by subject's clinical state or other factors.

**POSSIBLE:** reasonable temporal relationship with drug treatment. Event could be explained by subject's clinical state or other factors.

**UNLIKELY:** poor temporal relationship with drug treatment. Event easily explained by subject's clinical state or other factors.

**UNRELATED:** the event occurs prior to dosing. Event or intercurrent illness is due wholly to factors other than drug treatment.

### **9.3 Recording and reporting of AEs, ARs, SAEs, SARs AND SUSARs**

All AEs, ARs, SAEs, SARs and SUSARs will be documented in the eCRF.

The adverse event reporting period will be from consent until the subject's final study visit. In addition, any untoward event that may occur subsequent to the reporting period that the Investigator assesses as possibly, probably or definitely related to the study drug medication will also be reported as an Adverse Reaction.

AEs, ARs, SAEs, , SARs and SUSARs may be directly observed, reported spontaneously by the subject or by questioning the subject at each study visit. These will be followed up until they are resolved or the

subject's participation in the study ends (i.e. until the final eCRF is completed for that subject). In addition, all serious adverse events assessed by the Investigator as possibly related to the investigational medication should continue to be followed even after the subject's participation in the study is over.

Such events should be followed until resolution, or until no further change can reasonably be expected. Deaths occurring more than 30 days after the final dose, which are considered to be unrelated to the study medication, should not be reported as a Serious Adverse Event.

SAEs should be reported immediately to the BSCTU.

All **SAEs** occurring from the time of **consent** until **30** days post cessation of trial treatment must be recorded on the SAE Form and emailed to the BSCTU immediately at [[contact]](mailto:[contact]), at least **within 24 hours** of the research staff becoming aware of the event.

For each **SAE** the following information will be collected:

- full details in medical terms and case description
- event duration (start and end dates, if applicable)
- action taken
- outcome
- seriousness criteria
- causality (i.e. relatedness to trial drug / investigation), in the opinion of the investigator
- whether the event would be considered expected or unexpected in relation to the Reference Safety Information.

Any change of condition or other follow-up information should be emailed to the Sponsor as soon as it is available or at least within 24 hours of the information becoming available. Events will be followed up until the event has resolved or a final outcome has been reached.

All SAEs assigned by the PI or delegate (or following central review by the CI) as both suspected to be related to IMP-treatment and unexpected will be classified as SUSARs and will be subject to expedited reporting to the Medicines and Healthcare Products Regulatory Agency (MHRA). The Sponsor will inform the MHRA and the REC of SUSARs within the required expedited reporting timescales.

See Appendix 3 for a Safety Reporting Flowchart.

The following are clinically important adverse reactions of moderate intensity or more occurring among patients receiving maraviroc at rates greater than rates in the comparator as set out in the SPC:

Tabulated list of adverse reactions (reference safety information)

The adverse reactions are listed by system organ class (SOC) and frequency. Within each frequency grouping, undesirable effects are presented in order of decreasing seriousness. Frequencies are defined as very common ( $\geq 1/10$ ), common ( $\geq 1/100$  to  $< 1/10$ ), uncommon ( $\geq 1/1000$  to  $< 1/100$ ), rare ( $\geq 1/10,000$  to  $< 1/1,000$ ) not known (cannot be estimated from the available data). The adverse reactions and laboratory abnormalities presented below are not exposure adjusted.

| System Organ Class                                        | Adverse reaction                                                                                                                                                      | Frequency |
|-------------------------------------------------------------------------|-------------------------------------------------------------------------------------------------------------------------------------------------------------------------------------|-------------------------|
| Infections and infestations                                             | Pneumonia, oesophageal candidiasis                                                                                                                                                  | uncommon                |
| Neoplasm benign, malignant and unspecified (including cysts and polyps) | Bile duct cancer, diffuse large B-cell lymphoma, Hodgkin's disease, metastases to bone, metastases to liver, metastases to peritoneum, nasopharyngeal cancer, oesophageal carcinoma | rare                    |
| Blood and lymphatic system disorders                                    | Anaemia                                                                                                                                                                             | common                  |
|                                                                         | Pancytopenia, granulocytopenia                                                                                                                                                      | rare                    |
| Metabolism and nutrition disorders                                      | Anorexia                                                                                                                                                                            | common                  |
| Psychiatric disorders                                                   | Depression, insomnia                                                                                                                                                                | common                  |
| Nervous system disorders                                                | Seizures and seizure disorders                                                                                                                                                      | uncommon                |
| Cardiac disorders                                                       | Angina pectoris                                                                                                                                                                     | rare                    |
| Vascular disorders                                                      | Postural hypotension                                                                                                                                                                | uncommon                |
| Gastrointestinal disorders                                              | Abdominal pain, flatulence, nausea                                                                                                                                                  | common                  |
| Hepatobiliary disorders                                                 | Alanine aminotransferase increased, aspartate aminotransferase increased                                                                                                            | common                  |
|                                                                         | Hyperbilirubinaemia, gamma-glutamyltransferase increased                                                                                                                            | uncommon                |
|                                                                         | Hepatitis toxic, hepatic failure, hepatic cirrhosis, blood alkaline phosphatase increased                                                                                           | rare                    |
|                                                                         | Hepatic failure with allergic features                                                                                                                                              | very rare               |
| Skin and subcutaneous tissue disorders                                  | Rash                                                                                                                                                                                | common                  |
|                                                                         | Stevens-Johnson syndrome / Toxic epidermal necrolysis                                                                                                                               | rare / not known        |
| Musculoskeletal and connective tissue disorders                         | Myositis, blood creatine phosphokinase increased                                                                                                                                    | uncommon                |

|                                                      |                            |          |
|------------------------------------------------------|----------------------------|----------|
|                                                      | Muscle atrophy             | rare     |
| Renal and urinary disorders                          | Renal failure, proteinuria | uncommon |
| General disorders and administration site conditions | Asthenia                   | common   |

Cases of osteonecrosis have been reported, particularly in patients with generally acknowledged risk factors, advanced HIV disease or long-term exposure to combination antiretroviral therapy (cART). The frequency of this is unknown.

Delayed type hypersensitivity reactions, typically occurring within 2-6 weeks after start of therapy and including rash, fever, eosinophilia and liver reactions have been reported. Skin and liver reactions can occur as single events, or in combination.

In HIV infected patients with severe immune deficiency at the time of initiation of combination antiretroviral therapy, an inflammatory reaction to asymptomatic or residual opportunistic infections may arise. Autoimmune disorders (such as Graves' disease and autoimmune hepatitis) have also been reported; however, the reported time to onset is more variable and these events can occur many months after initiation of treatment.

Cases of syncope caused by postural hypotension have been reported.

